#### Confidentiality

2.13.3

To ensure participant privacy, this study will adhere to the *Personal Information Protection Law of the People’s Republic of China* and relevant regulations, implementing the following measures:

##### Categorized and hierarchical management

2.13.3.1

Participant identifiers (e.g., names, ID numbers), health information, and contact details will undergo classified hierarchical management with labeled organization. This ensures data of varying sensitivity levels receive commensurate security protection.

##### Encrypted data transmission

2.13.3.2

Encryption protocols will be implemented during data transmission. Decryption keys will be securely transmitted to recipients through separate, authenticated channels.

##### Encrypted storage

2.13.3.3

Personal information will be stored in encrypted form, adhering to national cryptographic management standards.

##### Segregation of biometric data

2.13.3.4

Where feasible, biometric information (e.g., fingerprints, facial recognition data) will be stored separately from personally identifiable information. Unless strictly necessary, raw biometric data will not be retained; only *cryptographic digest information* will be preserved.

### Investigator responsibilities

2.14

Researchers hold important responsibilities in clinical trials, including ensuring compliance with ethical and scientific standards, protecting subjects’ rights, maintaining data integrity, overseeing trial implementation, and promptly reporting adverse events. Additionally, all participating team members must undergo regular training and supervision to ensure strict adherence to the study protocol and relevant regulations, and to standardize and accurately collect data.

### Approval of trial protocol and amendments

2.15

This study will follow the *Ethical Review Measures for Biomedical Research Involving Human Subjects* and the ethical review and clinical trial management regulations issued by the National Health Commission. The trial protocol and informed consent form will be submitted to the Ethics Committee for review before the start of the trial, and require written approval. Any modifications to the trial protocol, including key changes in research design, subject population, sample size, etc., must be submitted in writing to the Ethics Committee before implementation. In urgent situations where deviations are necessary to eliminate an immediate hazard to subjects, the researcher may act first but must immediately report the deviation with justification to both the Ethics Committee and the sponsor. All protocol modifications and approval records will be securely archived to ensure trial transparency and regulatory compliance.

### Data monitoring

2.16

A Data Monitoring Committee (DMC) will be established for this study, consisting of at least 2 members of the Medical Ethics Committee of Dongying City People’s Hospital. The DMC will work according to a pre-established Data Monitoring Plan (DMP) and will be responsible for periodic assessment of the progress and safety data of the trial. Functioning independently and separately from the research team, its primary responsibilities include monitoring data integrity, evaluating subject safety, and safeguarding participant rights. All monitoring activities were performed in a blinded manner to ensure objectivity of data and reliability of trial results. If any non-compliance with the approved study protocol or any unauthorized changes in study procedures are discovered, the DMC has the right to immediately suspend or terminate the study. The final trial dataset will be accessible to the principal investigator, co-investigators, and sponsor-designated personnel, while also remaining available for review by the DMC and external auditors.

### Safety

2.17

Adverse events (AEs) in pregnant participants will be monitored throughout the intervention period, including but not limited to psychological reactions, mood fluctuations, behavioral changes, and difficulties with technology usage. All AEs will be recorded in detail, encompassing severity, time of onset, duration, interventions applied, and final outcomes. Any serious adverse events (SAEs) identified will be reported in accordance with the regulations and time requirements of the Medical Ethics Committee of Dongying People’s Hospital in Shandong Province. For urgent SAEs, the research team will immediately take necessary medical measures and promptly notify the Ethics Committee and the sponsor. The study will continuously evaluate the safety and applicability of interventions to ensure maternal safety and well-being, thereby generating critical safety data for the clinical trial.

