#### Inclusion criteria

2.4.1

(1) gestational age of 12 weeks (within a one-week window); (2) age of 18 years or older; (3) absence of plans for pregnancy termination; (4) commitment to reside in Shandong for at least one year and availability for study follow-up (with all visits conducted at Dongying People’s Hospital until delivery); (5) EPDS-Dep-5 score of ≥ 4 during depression screening (51); (6) consistent presence of a designated companion throughout pregnancy; and (7) comprehensive understanding and voluntary participation in the trial by both pregnant women and their companions (informed consent).

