### Interventions

2.7

The intervention content is grounded in mindfulness-based interventions (MBIs) and consists of six weekly themes designed to foster positive psychological states and healthy lifestyle routines among pregnant women. It integrates elements of the Individual and Family Self-Management Theory (IFSMT) and mobile-health strategies by leveraging the video-recording function of the WeChat app on smartphones: participants, accompanied by family members, record mindfulness videos on the assigned themes.

The multidisciplinary research team comprises one obstetrician, one obstetric nurse, and two research assistants. The obstetrician primarily handles maternal sudden illnesses and adverse reactions during pregnancy, while the obstetric nurse delivers positive thinking training tailored to specific intervention topics each week and addresses nursing and healthcare needs and precautions for pregnant women. The research assistants undertake various tasks, including registering study participant information, distributing and collecting questionnaires, disbursing subsidies. They also organize WeChat online video communications, downloading accompanying videos, and coordinating study follow-up visits.

The six-week Family Accompaniment Positive Thinking Intervention Program included six themes: 1) Understanding the Mindfulness-based Interventions Based on Family Accompaniment; 2) Speaking out about worries during pregnancy and childbirth; 3) How to better cope with adverse emotions during pregnancy and childbirth; 4) Familiarizing with the hospital’s maternity check-up process; 5) Each other in our eyes; and 6) Learning about maternal health. The specific intervention topics are detailed in **Table 1**.

**Table 1 T1:** Detailed Description of Intervention Themes.

Item	Theme	Explanation	Content of Implementation	Feedback

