6	Understanding Delivery	Help pregnant women recognize the delivery process, alleviate anxiety, enhance confidence, improve self-care awareness, actively participate in delivery, ensure maternal and infant safety, and make informed decisions to smoothly welcome the infant.	(1) Detailed introduction to the three stages of labor: cervical dilation stage, fetal delivery stage, and placental delivery stage, as well as possible situations and pain experiences in each stage; (2) Educational courses and lectures: Organize or recommend pregnant and puerperal women to participate in educational courses and lectures about the delivery process; (3) Watch educational videos: Provide educational videos about the delivery process for pregnant and puerperal women.	Send videos about "Understanding Delivery."

The intervention program comprised six themes, and each theme lasted a week and delivered via WeChat. It involved teaching on specific themes and filming videos. At the beginning of each week, the obstetric nurse presented the week’s theme content to the pregnant woman and her companion. She also provided relevant introductory materials, such as texts and videos. Pregnant women and their companions were asked to record a companion video related to family support for each theme and send it to the research group’s WeChat. Research assistants managed the videos to ensure they met the study criteria, and they will provide feedback when necessary. At the end of each week, there was a WeChat online video exchange where pregnant women and companions could ask the research team about perinatal clinical and nursing problems encountered during the week, and the team responded individually. Additionally, pregnant women completed a questionnaire via WeChat at each follow-up site.

The inclusion criteria for companion videos required both the pregnant woman and caregiver to appear in the video. They needed to describe and record content based on the weekly theme. Additionally, at least three companion videos had to be completed during the six-week intervention period, with each video filmed at intervals of one week or more. Exclusion criteria for companion videos included: repeated sharing of the same video; presence or speech by only one person; and videos shorter than one minute.

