### Control group

2.9

Pregnant women in the control group receive perinatal health care materials prepared by obstetricians and obstetric nurses. These materials, provided weekly as text messages, images, or both via WeChat, are sent during the first six weeks after enrolment. Additionally, the research assistant sends reminders via WeChat to prompt them to complete questionnaires at each follow-up time point.

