### Follow-up

2.11

This study will last for eight months. All participants, both in the intervention and control groups, are required to complete five follow-up assessments: baseline, mid-intervention at 15 weeks of pregnancy, end of intervention at 18 weeks of pregnancy, 36 weeks of pregnancy, and 4 weeks postpartum. The content of these follow-up assessments varies according to the time point. Demographic information is collected only at baseline; behavioral data, clinical test results (such as blood pressure and glucose levels), and questionnaire responses are collected at all follow-up points. Specific details of the information collected at each follow-up are shown in **Table 2**.

**Table 2 T2:** Follow-up Study Table.

Study period	Recruitment	Baseline	Intervention			
Timepoint		0w±1w (T1)	3w±1w (T2)	6w±1w (T3)	24w±1w (T4)	After delivery 4w±1w (T5)
Informed consent	✓					
Random grouping		✓				
Companion video sharing intervention		✓	✓	✓		
Send health-related text or images		✓	✓	✓		
Sociodemographic information		✓				
Behavioral information		✓	✓	✓	✓	✓
Medical history, physical examination (blood pressure, body height, weight, waist circumference), laboratory examinations (blood biochemistry, routine urine test).		✓	✓	✓	✓	✓
EPDS-Dep-5	✓	✓	✓	✓	✓	✓
GAD-7		✓	✓	✓	✓	✓
PSS		✓	✓	✓	✓	✓
PSQI		✓	✓	✓	✓	✓
FSS		✓	✓	✓	✓	✓
FHS-SF		✓	✓	✓	✓	✓
PSSS		✓	✓	✓	✓	✓
CBF-PI-B		✓				

The full name of EPDS-Dep-5 is the simplified version of the Edinburgh Postnatal Depression Scale; The full name of GAD-7 is Generalized Anxiety Disorder scale; The full name of PPS is Perceived Stress Scale; The full name is PSQI is Pittsburgh Sleep Quality Index; The full name of FSS is Fatigue Severity Scale; The full name of FHS-SF is The Family Health Scale short-form; The full name of PSSS is Perceived Social Support Scale; The full name of CBF-PI-B is The Chinese Big Five Personality Inventory Brief Version.

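### Adverse-event monitoring is stated for the intervention period, which ends at 18 weeks of pregnancy, so systematic event recording is not planned for about 80% of follow-up

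*Protocol article*

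**What the plan says.** Section 2.17 (Safety) gives one window for adverse events: "Adverse events (AEs) in pregnant participants will be monitored throughout the intervention period". It then lists what is recorded for each event (severity, onset, duration, interventions applied, outcome). Serious events that are identified are to be reported under the ethics committee's rules, with no end date. The section closes by saying that safety is evaluated continuously and that critical safety data will result.

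The intervention period is fixed elsewhere. Section 2.7: "The intervention program comprised six themes, and each theme lasted a week and delivered via WeChat". Section 2.9 gives the control group's weekly materials the same length; they "are sent during the first six weeks after enrolment". Section 2.11 lists the later assessments as "end of intervention at 18 weeks of pregnancy, 36 weeks of pregnancy, and 4 weeks postpartum", and Table 2 ticks the two intervention rows at T1 to T3 only.

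Data collection goes on after that. Section 2.11 says that "clinical test results (such as blood pressure and glucose levels), and questionnaire responses are collected at all follow-up points". Table 2 ticks medical history, physical examination, laboratory tests, EPDS-Dep-5 and GAD-7 at T4 and T5.

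**The concern.** The window for adverse events closes when the intervention does, yet the trial looks for benefit well beyond that point. The Background names depressive symptoms 4 weeks after delivery as the long-term effect of interest, and the Discussion expects evidence on long-term effects. Benefit would be measured to T5, while harm would be recorded in a structured way only to T3.

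The women are selected for raised depression risk (EPDS-Dep-5 of 4 or more, Section 2.4.1). Several of the events named in Section 2.17, such as psychological reactions and mood changes, are not tied to the six active weeks. If recording follows the text, the two groups cannot be compared on adverse events in late pregnancy, around delivery or postpartum. A statement that no safety signal was seen would then rest on roughly one fifth of the observation time.

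**Working it through.** **Inputs**
- Enrolment at 12 weeks of pregnancy, with a one-week window (Section 2.4.1), read here as 11 to 13 weeks.
- Six themes of one week each, so 6 weeks of intervention (Section 2.7).
- T2, T3 and T4 at 3, 6 and 24 weeks after baseline; T5 at 4 weeks after delivery (Table 2).
- Stated study length of eight months (Section 2.11).
- Week of delivery: not given in the document. **Assumption:** 40 weeks, with a range of 37 to 42.

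**The plan's own timeline**
- T2 = 12 + 3 = 15 weeks; T3 = 12 + 6 = 18 weeks; T4 = 12 + 24 = 36 weeks. All three agree with Section 2.11.
- Baseline to T5 = (delivery week − 12) + 4 = (40 − 12) + 4 = 32 weeks. At 4.345 weeks per month this is 7.4 months, which fits the stated eight months as a rounded figure.

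**Share of follow-up outside the stated window**

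Share outside = 1 − 6 / (delivery week + 4 − enrolment week)

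| Delivery | Enrolment | Follow-up (weeks) | Inside | Outside |
|---|---|---|---|---|
| 40 | 12 | 32 | 6/32 = 18.8% | 26/32 = 81.3% |
| 37 | 13 | 28 | 6/28 = 21.4% | 78.6% |
| 42 | 11 | 35 | 6/35 = 17.1% | 82.9% |

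With the stated eight months in place of an assumed delivery week: 8 × 30.4375 / 7 = 34.8 weeks, and 1 − 6/34.8 = 82.8% outside. If the end of intervention moves within the one-week tolerance of T3, the 32-week case gives 1 − 7/32 = 78.1% to 1 − 5/32 = 84.4%.

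**What the later visits supply**
- T3 and T4 are 36 − 18 = 18 weeks apart. With delivery at 40 weeks, T4 and T5 are 44 − 36 = 8 weeks apart.
- Scales and tests at T4 and T5 describe a woman's state around the visit. They do not give the onset, duration, action taken and outcome that Section 2.17 asks for, and an event that begins and resolves between visits may leave no trace in them.
- Medical history at T4 and T5 could pick up some such events, but the article does not say that it serves as an adverse-event record.

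**The case against.** A reader might infer that no safety data are planned after week 18, or that a worsening or a serious event would go unseen. The documents do not support either.

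- Depression and anxiety are study outcomes, measured in both groups at T4 and T5 together with medical history, examination and laboratory tests. Sustained worsening of mood would show there.
- Reporting of serious events has no stated end. Section 2.7 adds that "The obstetrician primarily handles maternal sudden illnesses and adverse reactions during pregnancy", which is not limited to six weeks.
- The data monitoring committee (Section 2.16) reviews safety data periodically under its own plan, which is not shown, and can see the final dataset. It cannot be said from the article that its record would be incomplete.
- An adverse-event form, or a row for it in the visit table, may sit in the full protocol. Its absence from the article is no finding.
- As extracted, the period label for intervention in Table 2 could span T2 to T5, which would widen the window. This may be an effect of the PDF reading.
- Tying routine event collection to exposure is a recognisable choice for a low-risk video and education programme, and one listed event, trouble with the technology, belongs mainly to the active weeks.

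Most of this stands, and it narrows the point to systematic adverse-event recording. It does not remove the point, because the article states a window rather than leaving it open. The wider reading of Table 2 would contradict both the ticks in that table and the 18-week end of intervention in Section 2.11. The sentence on serious events covers those that are identified, and no routine for identifying adverse events is stated after week 18.

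**Conclusion.** The point holds in limited form. As written, systematic adverse-event recording covers about 6 of 32 weeks and is not planned for about 80% of follow-up. The range is 79% to 83% under the assumed delivery and enrolment weeks, and the conclusion does not turn on where in that range the truth lies. The uncovered part includes late pregnancy, delivery and the postpartum period, which sits badly with the promise of continuous evaluation in the same section.

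The percentage is a share of calendar time, not of safety information lost. It rests on taking the intervention period to be the six weekly themes, as Sections 2.7 and 2.11 and the ticks in Table 2 define it. Sample size, power and the primary comparison are untouched. This is a cheap improvement in how harms are ascertained.

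**What to change.** Reconcile Section 2.17 with Section 2.11. State the recording window for adverse and serious adverse events as randomisation through T5 in both groups. Collect them with the same questions in each group at the existing T4 and T5 visits, asking about the time since the previous visit, and summarise them by randomised group. If the sponsor prefers to keep the present window, say so explicitly and limit any safety conclusion to the six intervention weeks.

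The cost is a change of wording, a short form at two visits that all 40 participants already attend, and some extra data entry. No visit is added and no analysis of efficacy changes.

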### Adherence and monitoring

2.8

The study adopted a multi-pronged approach to improve compliance with the intervention protocol. First, a dedicated prenatal education program was established to provide participants with a comprehensive curriculum, ensuring they understood the objectives and procedures of the intervention. Second, participants in the intervention group were supported by a specialized research team; the project team regularly sent notifications and responded to questions from pregnant women. Third, participants were notified by SMS and telephone each intervention week to prompt them to engage with video intervention content on specified topics at predetermined times. Finally, we implemented six weeks of interventions on different topics based on common issues encountered during pregnancy and enhanced compliance by increasing the diversity of interventions and participants’ interest in participation.

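### Adverse-event data are at risk of differential ascertainment: weekly live contact in the intervention arm, none described for controls, and no common adverse-event question scheduled

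*Protocol article*

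**What the plan says.** **Safety (2.17).** AEs among the pregnant women are watched for as long as the intervention runs. The types named are given as "including but not limited to psychological reactions, mood fluctuations, behavioral changes, and difficulties with technology usage". The section fixes what is recorded for each event (severity, onset, duration, action taken, outcome). It does not say how events come to the team's notice. It promises a continuing evaluation of the safety of the interventions but names no by-arm comparison.

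**Contact with the intervention arm (2.7 and 2.8).** Each of the six weeks opens with a nurse session: "At the beginning of each week, the obstetric nurse presented the week’s theme content to the pregnant woman and her companion". Each closes with live contact: "At the end of each week, there was a WeChat online video exchange where pregnant women and companions could ask the research team". In addition, "participants in the intervention group were supported by a specialized research team; the project team regularly sent notifications and responded to questions from pregnant women". Weekly prompts are also described: "participants were notified by SMS and telephone each intervention week to prompt them to engage with video intervention content". That last sentence names no arm, but only the intervention arm has video content to engage with.

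**Contact with the control arm (2.9).** Controls receive health care materials: "These materials, provided weekly as text messages, images, or both via WeChat, are sent during the first six weeks after enrolment". A research assistant also sends WeChat reminders to fill in questionnaires at the follow-up time points. No live exchange is described.

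**Contact common to both arms (2.11, Table 2).** There are five assessments. T1, T2 and T3 fall at 0, 3 and 6 weeks, within the intervention period. At each, both arms complete EPDS-Dep-5, GAD-7 and other scales and give medical history. The Follow-up section refers to Table 2 for the details of what is collected at each point, and that table has no AE row.

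**The concern.** Mood fluctuations and psychological reactions come to light when someone talks with the woman. The intervention is built to make her talk. In Table 1, theme 2 has her voice worries about pregnancy and childbirth, and theme 3 deals with coping with bad moods. The Discussion argues that passively received interventions limit emotional expression and that video sharing increases feedback to the team. On the protocol's own reasoning, then, the team will hear more from one arm than from the other.

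The technology item adds to this. Both arms use WeChat, but only intervention women must film, check and send videos. The item therefore partly measures exposure to the intervention.

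What is at stake is the safety statement that the Safety section promises. In a two-arm randomised trial, AE counts will naturally be read by arm. An excess in the intervention arm could come from more frequent contact rather than more harm, and no later analysis can separate the two if the events were not collected in the same way.

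**Working it through.** The Safety section gives no figure, so there is nothing to reproduce. The check sets the contact schedules side by side and then illustrates the possible effect on assumed values.

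**Step 1. Contact after baseline within the six-week window**

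| Contact | Intervention | Control | Source |
|---|---|---|---|
| Shared assessments (T2, T3) | 2 | 2 | 2.11, Table 2 |
| Live weekly video exchange | 6 | 0 described | 2.7; 2.9 |
| Nurse theme presentation (live or not is not stated) | 6 | 0 described | 2.7; 2.9 |
| SMS and telephone prompts on video content | weekly | none described | 2.8 |
| Common AE question | 0 in Table 2 | 0 in Table 2 | Table 2 |

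Counting only shared assessments and live exchanges, an intervention woman has 2 + 6 = 8 occasions on which an event could surface. A control woman has 2.

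**Step 2. What unequal capture would do (assumptions, not figures from the article)**

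Let the true risk *p* be the same in both arms, and let *c*₁ and *c*₀ be the probabilities that an event is recorded in the intervention and control arms. With 20 women per arm:

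- expected recorded cases = 20 × *p* × *c*
- apparent risk ratio = (*p* × *c*₁) / (*p* × *c*₀) = *c*₁ / *c*₀, which does not depend on *p*

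For *p* = 0.30, *c*₁ = 0.9 and *c*₀ = 0.5: 20 × 0.30 × 0.9 = 5.4 against 20 × 0.30 × 0.5 = 3.0, a ratio of 1.80. The range, with *c*₁ fixed at 0.9:

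| *c*₀ | Apparent ratio | Expected cases at *p* = 10% / 30% / 50% | Fisher's exact test below 0.05, % of trials at *p* = 10% / 30% / 50% |
|---|---|---|---|
| 0.9 | 1.00 | 1.8 v 1.8 / 5.4 v 5.4 / 9.0 v 9.0 | 0.96 / 2.40 / 2.15 |
| 0.7 | 1.29 | 1.8 v 1.4 / 5.4 v 4.2 / 9.0 v 7.0 | 0.90 / 3.67 / 5.39 |
| 0.5 | 1.80 | 1.8 v 1.0 / 5.4 v 3.0 / 9.0 v 5.0 | 1.13 / 8.67 / 17.91 |
| 0.3 | 3.00 | 1.8 v 0.6 / 5.4 v 1.8 / 9.0 v 3.0 | 1.63 / 20.74 / 44.31 |

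A formal test would seldom turn such a difference into a significant result unless events are common and capture is very unequal. The practical risk lies in descriptive counts, where a handful of extra recorded events can look like a signal with no true difference behind it.

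**The case against.** Several points on the other side stand.

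- **No collection route is stated.** A reader might infer that AEs are picked up through the weekly exchanges. The article does not say so. It describes those sessions as a chance to raise clinical and nursing questions.
- **No between-arm AE comparison is stated.** The Statistical methods section (2.12) compares follow-up indicators by GEE and does not mention AEs. A reader might call the safety comparison biased by design, but the text does not commit to such a comparison.
- **Control deterioration would not simply be missed.** Both arms complete EPDS-Dep-5, GAD-7 and medical history at the same times, so worsening mood in controls is measured. It might still be under-recorded as an AE.
- **The listed item is technology use in general.** Reading it as video technology narrows the text, since controls also use WeChat and QR-code questionnaires. The larger exposure is nonetheless in the video arm.
- **The article condenses a fuller protocol.** A common AE form or a detailed data monitoring plan may exist there, so a missing form alone would be no finding. What remains rests on stated features: unequal contact, an AE list that overlaps the intervention's content, and a collection schedule presented as specific that has no AE item.

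The objection therefore removes the stronger claims but not the risk.

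**Conclusion.** The point holds in a limited form. During the window in which AEs are monitored, contact is more frequent and more interactive in the intervention arm, and no common AE question is scheduled. The safety data are therefore at risk of differential ascertainment, most plausibly towards more recorded events in the intervention arm.

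The size of any bias cannot be computed from the article. The ratios of 1.29 to 3.00 rest wholly on assumed capture probabilities and equal true risk. The conclusion also assumes that AE counts will be read by arm, which the article does not state but a randomised safety report invites. This is a modest defect with a cheap remedy, and it does not affect the efficacy analysis.

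**What to change.** 1. Add one short AE question set, worded identically for both arms, to the shared online questionnaires at T2 and T3, and add a matching row to Table 2. These two visits fall within the stated AE window. Use T4 and T5 only if the safety window is deliberately extended, and then say so in the Safety section.
2. Base any by-arm AE summary on that source alone.
3. List events learned only through weekly exchanges, calls or videos separately, as information from the intervention arm. They remain recorded and reported under the existing safety rules.
4. Report technology difficulties as a feasibility item outside the comparative AE rate. Section 2.10.2.2 already asks about trouble with operating the video recording, so a place for them exists.

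The cost is a few items on an existing form, a reporting rule and about a minute of extra burden per visit.
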